### Assessment of potential moderator variables

At the beginning of the study, demographic data like age, sex, and level of education are documented. Furthermore, the (German version of the) Multiple-Choice Vocabulary Intelligence Test (MWT-B; Lehrl, 1999) measures crystallized intelligence, a sociodemographic measure that is not expected to change after the intervention. To control for acute psychological conditions during the pre-and post-assessments as well as general personality traits, questionnaires are filled out. These include the (German versions of the) Beck Depression Inventory Revision (BDI-II; Beck et al., 1996), the Big-Five-Inventory (BFI-10; Rammstedt et al., 2013), the measurement of everyday cognition (ECog; Farias et al., 2008), the Hospital Anxiety and Depression Scale (HADS-D; Herrmann-Lingen et al., 2018), the Memory Functioning Questionnaire (MFQ; Gilewski et al., 1990), and the Patient Health Questionnaire (PHQ-9; Gräfe et al., 2004). The questionnaires are normed, standardized, and validated German versions of established questionnaires. The only exceptions are the ECog and the MFQ, for which no official German version was available and which we translated for this study. Data from these questionnaires will be used in an exploratory manner.

### MRI data acquisition

All assessments take place on a 3.0-T MR scanner (Trio, Siemens, Erlangen, Germany) to obtain echo-planar T2*-weighted image volumes (EPI) and transaxial T1-weighted structural images. Functional resting state data are acquired in one EPI session of 250 volumes. The first three volumes will be subsequently discarded due to equilibration effects. A functional-image volume comprises 100 transaxial slices including the whole cerebrum and cerebellum (voxel size = 1.4 mm × 1.4 mm × 1.4 mm, repetition time, TR = 1950 ms, echo time, TE = 33.6 ms).

T1-weighted anatomical 3D images are collected with the same MR scanner. The following scan parameters are used: TR = 2.25 s, TE = 3.03 ms, inversion time, TI = 900 ms, field of view, FoV = 256 × 256 mm2, flip angle = 9°, voxel resolution = 1 × 1 × 1 mm^3^, and 176 axial slices.

For Diffusion Tensor Imaging, the following parameters are used: TR 3318 ms, TE 87.40 ms, FoV 210 mm, flip angle 78°, voxel size 1.5 × 1.5 × 1.5 mm^3^, slices 96, first anterior to posterior, then vice versa.

### Microbiome data acquisition

At the first appointment of the pre-and the post-assessment, a stool collection tube (INVITEK Stool Collection Tubes with DNA Stabilizer, #1038111200, Berlin, Germany) is handed to the participants together with a stool collector (MED + ORG Stuhlauffanghilfe, Niedereschach, Germany). Participants have to collect the fecal sample at home according to the enclosed instructions and return the tube on one of the next pre-assessment appointments. They are advised to collect the post-assessment stool sample at an equal time of the day as the pre-sample in order to keep the two samples comparable. Furthermore, samples should be collected as close as possible to the day they are handing the sample in, even though the DNA stabilizer conserves the sample for up to 3 months at room temperature. Stool samples are then taken to the Integrated Biobank Jena of the JUH and frozen at −80°C.

### Sports data acquisition

At first, general anthropometric measures (body mass, height, hip and waist circumferences) as well as assessments of heart rate and heart rate variability are taken during resting conditions. After that, there are three approaches used to estimate the cardiorespiratory fitness (CRF) of a participant.

First, after an introduction to Borg’s scale of perceived exertion (RPE 6–20 scale; Borg, 1970), participants undergo a submaximal bicycle ergometer test, according to the test procedure after Ekblom-Bak et al. (2014; Björkman et al., 2016), in order to estimate their maximum oxygen uptake (VO_2_max). The test is performed on an electronically braked cycle-ergometer (ergoselect 100^®^, Ergoline, Bitz, Germany) in a climate-controlled laboratory environment. Participants are instructed to pedal at a cadence of 60 to 65 RPM and not to speak or adjust the position for the duration of the test. The total duration of the test is 8 min, with the initial 4 min performed at a low fixed power output of 30 watts, directly followed by 4 min at a higher individualized power output (aiming at an RPE of ≈14 on the Borg 6–20 scale). RPE is inquired in the second, third, and fourth minute of the two exercise stages. The heart rate of the participants is constantly measured throughout the test and capillary lactate blood samples are taken at rest, in the last minute of the first and second stages, as well as one and 3 mins after cessation of the test. Using sex-specific prediction equations (Björkman et al., 2016), VO_2_max can be predicted based on the independent variables age, change in HR per unit, change in power output, the difference in work rates, and HR at standard work rate. This submaximal cycle ergometer test and the underlying prediction model were developed on the basis of a graded maximal treadmill test. The adjusted *R*^2^ for this model are 0.81 (SEE = 0.31 L min^−1^) for ages between 50 and 64, and 0.81 (SEE =0.25 L min^−1^) for people older than 65 years. While measuring VO_2_max using maximal testing remains the most accurate approach, we decided to conduct a submaximal bicycle ergometer test, as we are testing older individuals. Undergoing a maximum exercise test could elevate the likelihood of adverse cardiac events (Arena et al., 2007; Sartor et al., 2013) and results are more prone to be biased by musculoskeletal impairments or motivation of a participant (Noonan and Dean, 2000).

The second test to estimate VO_2_max is the 6-min walking test, in which participants have to walk as fast and far as they can on a specified 20-meter route (Mänttäri et al., 2018). Heart rate is constantly measured, and distance is tracked. After the 6 mins, participants are instructed to rest, and blood samples as well as subjective exhaustion scores are taken one and 3 mins after the trial ends.

At last, a non-exercise-based prediction model is used, specifying sports habits, anthropometric measures, and resting sitting heart rate to estimate a person’s VO_2_peak (Nes et al., 2011).

As the study protocol was developed at a time when potential changes in COVID-19 regulations had to be taken into account, we are using three different methods to estimate CRF in terms of VO_2_max and VO_2_peak, respectively. Both the non-exercise-based prediction model and the 6-min walking test could be conducted without the need for a laboratory and while keeping the required minimum distance to the participants. In case we are able to conduct all three tests with all participants and the estimates end up differing from each other, we will use the results of the submaximal bicycle ergometer test because it allows the most accurate estimation of VO_2_max.

After all tests estimating CRF are finished, participants’ handgrip strength is measured with a calibrated Jamar^®^ Smart digital hand dynamometer (Performance Health, Warrenville, IL), according to Southampton protocol for adult grip strength measurement (Roberts et al., 2011). The measurement is conducted in a standardized sitting position, upper arm close to the upper body, and the elbow flexed at a 90° angle. Maximum isometric strength is measured three times (alternating) for both hands and the highest value attained by each hand as well as the overall maximum is used for further calculation.

### General procedure

After the successful recruitment of a participant, dates for the pre-assessment are scheduled. The pre-and post-assessment consist of three appointments at three different locations, respectively. Figure 2 shows the procedure flowchart. Before their first appointment, participants receive detailed written information about the study via mail. To preclude the risk of cardiovascular incidents during the self-monitored intervention, all participants have to undergo a checkup examination beforehand. This checkup can be done either by their general practitioner or by the study physician during the first session at the clinic.

**Figure 2 fig2:**
[figure not shown]
Flow diagram of the study. MRI, Magnetic Resonance Imaging; ACE-III, Addenbrooke’s Cognitive Examination III.

The pre-assessment comprises three different sessions. The “NPT session” at JUH, the “Sports session” at the Sports Medicine Department of Friedrich-Schiller University Jena, and the “MRI session” at the JUH research scanner. Every session takes place on a different day and the order in which they are held is not predefined. The only exception is made when participants have a very long drive to Jena. In that case, the MRI session is planned for the same day as the NPT session so that participants only have 2 days on which they have to come to Jena. In general, the three sessions are planned to take place within a maximum of 2 weeks in order to keep the total duration of the study and the time interval between the pre-and the post-assessments as similar as possible between all participants.

In the beginning of the first session, participants have the opportunity to ask questions about the content and procedure of the study. If they agree with all aspects, they sign the informed consent. Also, as described above, a stool collection tube is handed out to each participant.

In the “NPT session,” the majority of the neuropsychological data is assessed. Tests conducted on that day include the Mars contrast sensitivity test, TVA whole and partial report, Addenbrooke’s Cognitive Examination, Mehrfachwahl-Wortschatz-Intelligenztest, and the Trail-Making-Test A-and-B. Furthermore, participants fill out questionnaires, including Becks Depression Inventory, Big Five Inventory, ECog Performance Status Scale, Hospital Anxiety and Depression Scale, Memory Functioning Questionnaire, and the Gesundheitsfragebogen für Patienten. All tests and questionnaires are always performed in the same order and take around 2 h in total.

The “MRI session” takes place at the JUH research scanner. On the MRI session, participants start by reading and signing the MRI information and consent. After that, they hold a pre-treatment consultation with a radiologist. If the radiologist gives his/her approval, the MRI assessment can be conducted. The MRI session consists of a short scout sequence, a structural brain scan, an fMRI resting state as well as a Diffusion Tensor Imaging sequence. Altogether, it lasts approximately 30 min.

The “Sports session” is completed at the Sports Medicine department of the Friedrich-Schiller University Jena. All sports measures are taken and remaining NPTs (VLMT, ROCF, FWIT) are conducted as described above. Furthermore, participants are instructed on how to conduct the intervention. All participants receive a code that grants access to the study website to their respective intervention group contents. The contents as well as general guidelines on how to conduct the intervention are explained. Lastly, the pulse watch (Garmin vivosmart 4) is handed to the participants and its functioning and handling are explained and tested. With the sports measures and tests, the NPTs, and the introduction to the intervention combined, this session takes between two and two and a half hours.

After finishing the pre-assessment, participants start with their intervention on Monday of the following week. All supplementary materials needed for the conduction (weekly unit overview, questionnaire links, instructions, videos, etc.) can be found on the study website. Both intervention groups are identical concerning their weekly expenditure of time. In the experimental intervention group, participants follow a multicomponent physical activity plan consisting of aerobic exercises (medium-intensity and medium-to-high-intensity walking units), balancing exercises (yoga), and coordination exercises (juggling). A detailed listing of all units and durations can be found in Figure 3. Every walking unit has a specific intensity rating, ranging from “1” (very low intensity) to “4” (high-intensity). For every intensity score, participants find advice on the study website on how to walk in this intensity as well as values from the Borg’s scale of perceived exertion, which they already know from the Sports session of the pre-assessment. The yoga lessons have been designed and recorded specifically for this study. While they can be assumed to entail aerobic parts, they focus on balancing and flexibility improvement for elderly. The aim of the experimental intervention is to increase maximum oxygen uptake in a wholesome and healthy way, as recommended by the World Health Organization and the American College of Sports Medicine (World Health Organization, 2007; Lee et al., 2017). In the active control group, participants listen to podcasts on different age-related scientific topics and perform progressive muscle relaxation exercises, which both have been recorded specifically for this study, at the medical department of the JUH and the sports department of the FSU, respectively. This control group is designed to let participants have the same time expenditure with their units as the experimental intervention group, without influencing their maximum oxygen uptake. Lastly, participants in both groups fill out a short questionnaire about sleep and activity behavior on a daily basis. All participants are instructed to do the units of their respective training plan on top of their existing sports habits so that baseline activity is maintained.

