**Methods and analysis:**

One-hundred healthy participants aged 60 to 75 years will be recruited. First, participants will undergo an extensive baseline assessment consisting of neurocognitive tests, functional and structural brain imaging, physical fitness tests, and gut-microbiome profiling. Next, participants will be randomized into either a multi-component physical activity group (experimental condition) or a relaxation group (active control condition), with each training lasting 8 weeks and including an equal number and duration of exercises. The whole intervention will be online-based, i.e., participants will find their intervention schedule and all materials needed on the study website. After the intervention phase, participants will have their post-intervention assessment, which consists of the same measures and tests as the baseline assessment. The primary outcome of this study is the change in the cognitive parameter of visual processing speed from baseline to post-measurement, which will on average take place 10 weeks after the randomization. Secondary outcomes related to cognitive, brain, and microbiome data will be analyzed exploratory.

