### Sample characteristics and recruitment

The inclusion and exclusion criteria for this study are listed in detail in Table 1. In brief, inclusion criteria comprise being at an age of 60 to 75 years, possessing a smartphone, having basic immunization against COVID-19 and being overall healthy. Exclusion criteria include specific non-communicable diseases, that affect the gut microbiome (e.g., diabetes, chronic obstipation, or diarrhea), that affect the ability to do sports or pose a risk when doing sports (e.g., stadium 3 and 4 cardiac diseases, and asthma), or that can affect cognition (neurological or psychiatric diseases). Intake of specific medication that might affect cognition or the gut microbiome composition lead to an exclusion, too. To ensure a risk-free MRI examination, contraindications for MRI are exclusion criteria as well (e.g., cardiac pacemaker and claustrophobia). A conspicuous value (≤86) in the cognitive screening test Addenbrooke’s Cognitive Examination III (ACE-III; Noone, 2015) is another exclusion criterion in order to exclude participants with signs of mild cognitive impairment and, thus, risk for a neurodegenerative process. Most exclusion criteria are checked in an interview before potential participants will be recruited. The cognitive status is assessed during the pre-assessment. Furthermore, a physician checks every participant before the self-monitored intervention to preclude any cardiovascular risks.

**Table 1 tab1:** Exclusion criteria for participants.

Relevant, uncorrected vision disorder
Evidence of cognitive impairment (ACE-III score of ≤86)
Relevant psychiatric or neurological pre-existing condition (e.g., major depression, focal damage of the brain due to operation or stroke, epilepsy)
Contraindications for MRI (e.g., cardiac pacemaker, non-removable metal parts in/at the body, claustrophobia)
Permanent medication with sedating substances
Loss of capacity of consent
Relevant, physical impairment
Stadium 3 and 4 cardiac diseases
Relevant systemic disease: cancer, severe kidney or liver disease, type 1 or 2 diabetes, diseases with intrinsic inflammation (e.g., arthritis, Crohn’s disease, asthma, chronic infections)
Treatments that influence glucose or microbiome composition: antidiabetics, antibiotics, immune suppressants, etc.
Chronic obstipation or diarrhea
Symptoms of clinical infection during the last month
Excessive alcohol/drug consumption
Severe eating disorder
Known disruption of iron balance

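### The group is disclosed in the Sports session, but the order of the pre-assessment sessions is open, so baseline VPS C and the ACE-III exclusion can follow disclosure

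*Protocol article*

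**What the plan says.** The abstract (Methods and analysis) places the full baseline assessment first and then continues: "Next, participants will be randomized into either a multi-component physical activity group".

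The General procedure divides the pre-assessment into an NPT, a Sports and an MRI session. On their sequence it says: "Every session takes place on a different day and the order in which they are held is not predefined". On their spacing: "In general, the three sessions are planned to take place within a maximum of 2 weeks". The one exception, for participants who travel far, puts MRI and NPT on the same day and does not say where Sports falls.

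The group is disclosed in the Sports session: "All participants receive a code that grants access to the study website to their respective intervention group contents". The text goes on: "The contents as well as general guidelines on how to conduct the intervention are explained".

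The primary outcome and the cognitive screen are in the NPT session: "Tests conducted on that day include the Mars contrast sensitivity test, TVA whole and partial report, Addenbrooke’s Cognitive Examination". Under Sample characteristics and recruitment, an ACE-III score of 86 or less is an exclusion criterion, and its timing is given as follows: "The cognitive status is assessed during the pre-assessment". The Data analysis plan uses baseline VPS C as a covariate in the confirmatory ANCOVA, together with sex.

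**The concern.** A code for the participant's own group cannot be issued before that participant has been allocated. Randomization must therefore come no later than the Sports session. Since that session may be first or second of the three, the procedure permits allocation and disclosure before the NPT session, which the abstract's sequence rules out.

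Two things are at stake. First, the ANCOVA covariate is then no longer guaranteed to be a pre-allocation value. If knowing the arm changes effort or expectation differently in the two groups, part of that difference enters baseline C and passes through the regression slope into the adjusted group effect. Second, a participant who fails the ACE-III after the Sports session has already been randomized, so the exclusion takes people out of the randomized set instead of screening them beforehand. Baseline TMT, questionnaires, MRI and the stool sample can follow disclosure in the same way, but they feed only secondary or exploratory analyses.

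**Working it through.** **1. The plan's own figure.** Inputs from Sample size: difference 3 letters/s, SD 5, power 80%, two-sided α = 0.05. The standardized difference is 3/5 = 0.6. The two-sample t-test solution is 44.59, so 45 per arm, as stated. Power is 80.4% at 45 and 84.4% at 50 per arm. No stated number is wrong; the problem is one of sequence.

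**2. What the text permits.**
- Allocation must precede the code, and the code is given in the Sports session.
- The Sports session may stand anywhere among the three.
- Baseline C and the ACE-III are in the NPT session.
- The physician check does not force a clinic visit before Sports, because it may be done by the participant's general practitioner (General procedure).
- The intervention starts on the Monday after the pre-assessment is finished. This fixes the start of training, not the moment of disclosure.
- The stool tube is handed out at the first appointment and returned at a later one (Microbiome data acquisition). If Sports comes first, the sample is necessarily taken after that session.

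**3. Counting the orders** (N = NPT, S = Sports, M = MRI): N-S-M, N-M-S, S-N-M, S-M-N, M-N-S, M-S-N.
- NPT after Sports: S-N-M, S-M-N, M-S-N = 3 of 6.
- MRI after Sports: N-S-M, S-N-M, S-M-N = 3 of 6.
- At least one of the two after Sports: 4 of 6.

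These are counts of permitted orders. The article does not say how often each occurs.

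**4. Illustration of bias (all inputs assumed).** Let d be the shift in baseline C caused by knowing the group, in one arm only, f the share of participants affected, and b the ANCOVA slope. Assume that the post-assessment value is not shifted. Then

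size of bias in the adjusted effect = b × f × d.

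- b = 0.7, f = 0.5, d = 0.5: 0.7 × 0.5 × 0.5 = 0.175 letters/s, or 0.175/3 = 5.8% of the planned difference.
- b = 0.7, f = 0.5, d = 1: 0.35 letters/s, or 11.7%.
- Lowest of the wider range (b = 0.5, f = 0.25, d = 0.5): 0.0625 letters/s, about 2%.
- Highest (b = 0.9, f = 0.5, d = 2): 0.90 letters/s, 30%.

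The sign is opposite to the baseline shift. A raised baseline in the exercise arm shrinks the estimated benefit, and a raised baseline in the control arm inflates it. For scale, the unadjusted standard error of the group difference at 50 per arm is 5 × √(2/50) = 1.0 letters/s.

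**5. Illustration of lost numbers (losses assumed).** If 2, 5 or 10 of the 50 per arm were excluded after randomization and not replaced, t-test power would be 82.9%, 80.4% or 75.5%. The article gives no expected ACE-III failure rate.

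**The case against.** The intended order is stated in the abstract, and the General procedure does not say when randomization happens. Figure 2, the flow diagram, is not visible here and may place it. The article is also a condensed account. On this view the defect is unreconciled wording, not proof that any baseline was taken after allocation. That stands as a limit: the text shows what is permitted, not what was done. It does not remove the conflict, because a figure with a fixed order would itself contradict the statement that the order is open.

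Participants are not told the hypotheses (Study design), and both arms are active with equal time commitment. This makes an arm-specific shift in baseline less obvious. It does not hide the arm, since the contents are explained. C is modelled from report accuracy without time pressure and is not a self-rating, which also argues for a modest shift.

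A reader might infer several stronger claims that the article does not support:
- **Staff know the arm.** Disclosure is described to the participant, at the sports medicine department. NPT and MRI take place at the university hospital, and nothing says that the examiner or radiologist is told.
- **Exclusions are made with the arm in view.** The ACE-III rule is a fixed cut-off. If arm knowledge does not affect the score, applying the rule late costs numbers but does not in itself favour an arm.
- **MRI clearance is a further post-randomization exclusion.** The text says only that the scan can proceed with approval. It does not say that refusal removes the participant, and most criteria are checked by interview before recruitment.
- **Participants train early.** They hold the code, but the stated start is after the pre-assessment.

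**Conclusion.** The concern holds as a conflict between the abstract and the General procedure that bears on the confirmatory analysis. As written, baseline C and the ACE-III exclusion can follow disclosure of the arm to the participant, and the ACE-III exclusion can become post-randomization. This conclusion rests only on the article's text and needs no outside figure.

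The size of the problem is not known. Half of the permitted orders put NPT after Sports, but reading that as half of the participants assumes equally likely orders. The 0.18 to 0.35 letters/s is an illustration on assumed values with no known direction, and the wider assumptions span 2% to 30% of the planned difference. The article supports no claim that the trial is biased by a given amount, or that exclusions will exhaust the sample. The point is worth fixing because the remedy is simple and protects the primary covariate.

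**What to change.** Reconcile the abstract with the General procedure in one of two ways:
- state that the Sports session is always the last pre-assessment session; or
- keep the order free, but randomize and release the access code only after the NPT session (baseline C and ACE-III), the MRI session and the stool sample are complete.

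Data collection was planned to start in March 2022. For participants already enrolled, record the session order and add a sensitivity analysis of the primary outcome limited to those whose NPT session preceded disclosure. This subset keeps the protection of randomization only if appointments were fixed before allocation, so the record should show that too. It will also be less precise: if it held half the sample, the unadjusted standard error would be 5 × √(2/25) = 1.41 instead of 1.0 letters/s.

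The cost is a scheduling rule, a sentence of protocol text and slightly less flexible appointment booking. The sample size and the primary model do not change.
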